### Trial objectives

The primary endpoint is defined as the occurrence of treatment-related gastrointestinal or hepatobiliary toxicity of grade III or higher according to Common Terminology Criteria for Adverse Events (CTCAE) V5.0 assessed within the first year after SBRT. The primary aim of the study is the assessment of non-inferiority of MRgRT to ITV-SBRT regarding the primary endpoint, assuming a non-inferiority margin of $$\delta =10\%.$$ Toxicity of CTCAE III° or higher is generally low, between below 1% [57] and 7.7% [46] according to published literature. Therefore, a non-inferiority-margin of $$\updelta$$=10% is deemed adequate.

Secondary objectives include further toxicity according to CTCAE V5.0, quality of life according to EORTC QLQ C-30 and EORTC QLQ LMC-21, local control (treated lesions), locoregional control (whole liver), distant tumor control, progression-free survival (PFS) and overall survival (OS).

QoL will be measured with the help of the validated 30-item self-assessment questionnaire of the European Organization for Research and Treatment of Cancer (EORTC QLQ-C30, version 3.0). It is composed of five multi-item functional scales (physical, role, emotional, cognitive, and social function), three multi-item symptom scales (fatigue, pain, nausea/vomiting) combined with a global health and quality-of life scale. The other six single items assess further symptoms (dyspnea, insomnia, appetite loss, constipation and diarrhea) that are often reported by cancer patients as well as financial difficulties [58]. The QLQ-C30 questionnaire will be complemented with the colorectal liver cancer module of the EORTC (QLQ-LMC-21), initially designed for patients with colorectal liver metastases [59, 60]. QLQ-LMC-21 comprises another 21 items in five scales (nutritional, fatigue, pain, emotional) and six single items assessing further symptoms (weight, loss of taste, xerostomia, oral mucositis, paresthesia, jaundice).

For patients in the MRgRT arms, an in-house developed patient-reported questionnaire will be applied after the first fraction of radiotherapy and at the end of radiotherapy to assess acceptance of MR-guided radiotherapy [53]. The questionnaire consists of questions regarding potential MR-related experiences and complaints (e.g. noise, bore size, fixation with coils). Furthermore, the perception of their active role during gated dose delivery SBRT is assessed. Items are scored using a 5-point scale.

MR-guided and ITV-based SBRT will be compared with respect to toxicity and local control, treatment plan and irradiation parameters including potential BED increase and OAR dose decrease using MRgRT as well as required adaption frequency and dosimetric benefit of adaption for MRgRT. Morphological and functional changes in MRI during and after radiotherapy will be evaluated, in particular with regard to dose distribution [61, 62]. Potential prognostic biomarkers such as plasma levels of hepatic growth factor (HGF) and interleukines (e.g. IL-6 and IL-8) will also be assessed [63].

### Study visits and follow-up

After screening of patients for inclusion and exclusion criteria, successful completion of breath hold assessment as well as having received informed consent, appropriate patients will be recruited to the trial.

Study relevant data will be collected and patient history will be assessed, including demographic data, medical history, physical examination, comorbidities and concomitant medication, laboratory evaluation including blood count, liver function parameters and potential biomarkers.

The baseline visit (T0) will be scheduled after trial inclusion and prior to the first fraction of SBRT. During the baseline visit (T0) a clinical assessment, as well as analysis of quality of life (using EORTC QLQ C-30 and EORTC QLQ LMC-21) is planned. Baseline symptoms and toxicities will be assessed according to CTCAE V5.0.

Further evaluations will be scheduled during SBRT (mid of treatment, T1), at the last day of treatment (T2), 6 weeks after radiotherapy (T3), every 3 months after radiotherapy during the first year (T4-7) and then every 6 months up to completion of a follow-up of at least 2 years (T8, T9). Study visits are also depicted in the flowchart and in Table 2.

**Table 2 Tab2:** Screening, treatment and follow-up visits

	Screening	Baseline (before SBRT)	Mid of SBRT	End of SBRT	Follow-up		
					6 weeks after SBRT	1st year after SBRT: every 3 months	2nd year after SBRT: every 6 months
		T0	T1	T2	T3	T4-7	T8-9
Medical history		x		x	x	x	x
EORTC QLQ-C30 and LMC21		x		x	x	x	x
MR-Linac questionnaire (only treatment arm A)		x		x			
Documentation of medication		x		x	x	x	x
Documentation of Adverse Events		x		x	x	x	x
Case report form		x		x	x	x	x
Blood test		x	x	x	x	x	
Breathhold assessment (> 25 s?)	x						
MRI (c = contrast enhanced, n = without)	x (c)		x (n)	x (n)	x (c)	x (c)	x (c)

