CTV, clinical target volume; D_xcm3_, dose which is received by less than × cm^3^

In a second step, patients to be treated with MRgRT receive a simulation at the MR-Linac for MRgRT planning. If necessary, they also undergo a specific planning CT in deep-inspiration breath-hold (non-contrast-enhanced). In the MRgRT arms, patients are immobilized in supine position, and fitted with the MRI receiver coils.

For MRgRT (arms A and C), target volume delineation is performed as follows:Gross tumor volume (GTV): macroscopic, contrast-enhanced tumor in the planning MR and, if definable, in the planning CTClinical Target Volume (CTV): GTV + 5 mmPlanning Target Volume (PTV): CTV + 3 mm

Dose prescription and constraints for MRgRT are the same as for ITV-based SBRT as described above. In arm A, a BED of ≥ 100 Gy must be prescribed. In arm C, patients are treated via MRgRT with the highest achievable dose as deemed by the treating radiation oncologist.

For MRgRT (arms A and C), daily OAR contour adaption is performed within the region PTV_expand_ slightly adapted from the recommendations by Bohoudi et al. [44]. The PTV_expand_ is the PTV enlarged by 3 cm in medio-lateral and anterior–posterior direction as well as 1 cm in the cranio-caudal direction. The need to adapt the treatment plan is decided upon by the treating physician based on dose prediction. For MRgRT, real-time cine MR imaging is used for respiratory gating. Gating thresholds are defined by the treating physician.

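### Table 2 and the text disagree on which arms complete the MR-Linac acceptance questionnaire and when its first reading is taken

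*Protocol article*

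**What the plan says.** Three places in the protocol article bear on this.

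- **Trial objectives** sets the population and the timing: "For patients in the MRgRT arms, an in-house developed patient-reported questionnaire will be applied after the first fraction of radiotherapy and at the end", meaning the close of treatment. On content it says: "The questionnaire consists of questions regarding potential MR-related experiences and complaints (e.g. noise, bore size, fixation with coils". It adds that "the perception of their active role during gated dose delivery SBRT is assessed".
- **Treatment planning and dose prescription** shows which arms are meant: "For MRgRT (arms A and C), target volume delineation is performed as follows". The Randomization section likewise assigns MRgRT to arm C.
- **Study visits and follow-up** contains Table 2, whose row reads "MR-Linac questionnaire (only treatment arm A" and carries marks under T0 and T2 only. The T0 column is headed as baseline before SBRT, and the accompanying text agrees: "The baseline visit (T0) will be scheduled after trial inclusion and prior to the first fraction of SBRT". That text describes T0 with the words "During the baseline visit (T0) a clinical assessment, as well as analysis of quality of life" and goes on to CTCAE baseline symptoms. It does not list the MR-Linac questionnaire there.

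**The concern.** The two statements differ on both things that define a data collection: who answers, and when. On arms, the text includes arm C and the table excludes it. On timing, the text places the first reading after a fraction and the table places it before any fraction. They agree only on the end-of-treatment reading in arm A.

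A visit table is an operative part of a plan, not background. If it governed data collection, acceptance in arm C would go unrecorded. Arm C is the group in which the Discussion hopes to show dose escalation, and the Background stresses how staff-intensive and time-consuming MRgRT is. The first arm A reading would also fail to capture the experience of treatment that the text sets out to measure. Patient-reported experience that is not collected at the time cannot be recovered reliably afterwards.

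**Working it through.** **Is the conflict real or an effect of text extraction?** The arm restriction consists of words inside the row label, so a shifted column cannot produce it. The two marks line up with T0 and T2 in the same way as in neighbouring rows. No amendment log is involved; both statements are current text.

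**Side by side**

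| | Trial objectives (text) | Table 2 |
|---|---|---|
| Arms | MRgRT arms, i.e. A and C | A only |
| First reading | after the first fraction | T0, before SBRT |
| Last reading | end of radiotherapy | T2, end of SBRT |

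Table 2 has no column for a visit after the first fraction. T1 is mid-treatment and carries no mark in this row. The reading that the text requires therefore has no place in the schedule.

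**What could be answered at T0?** The article names four topics.

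- Noise, bore size and coil fixation: MRgRT patients have a simulation at the MR-Linac, and in the MRgRT arms they are fitted with receiver coils. T0 may fall anywhere between inclusion and the first fraction. If it follows simulation, which the article does not say, these items could be answered from that session.
- Active role during gated dose delivery: this needs a delivered fraction and cannot be answered at T0 in any case.

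**How many patients are affected?** Inputs from Statistical analysis, Randomization and Trial design: 62 patients for arms A and B, allocation 1:1, at least 20 analyzable patients in arm C, at least 82 in total.

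1. The 62 reproduces. The Farrington-Manning formula is n per arm = [(z₀.₉₀·s₀ + z₀.₈₀·s₁) / (δ − (p_A − p_B))]², with p_A = 0.02, p_B = 0.05 and δ = 0.10.
   - The restricted estimates under the null are 0.1258 and 0.0258, so s₀ = √(0.1258·0.8742 + 0.0258·0.9742) = 0.368.
   - s₁ = √(0.02·0.98 + 0.05·0.95) = 0.259.
   - n = [(1.2816·0.368 + 0.8416·0.259) / 0.13]² ≈ 28.1, so 29 per arm and 58 in total.
   - Allowing for 5% loss, 58/0.95 = 61.05, rounded up to 62.
2. 62 + 20 = 82, which matches the stated total.
3. Arm A: 62/2 = 31. MRgRT patients: 31 + 20 = 51.
4. Share omitted under the table: 20/51 = 39%. With arm A at 29, before the loss allowance, it is 20/49 = 41%.

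The share is approximate. Both sizes are minimum targets, and recruitment continues until arm C is filled. Further arm A patients would lower the share, and further arm C patients would raise it.

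The sample-size step only supplies the arm sizes. The contradiction itself does not depend on it.

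**The case against.** The inconsistency itself is hard to dispute. The case on the other side concerns its consequences.

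- **A reader might infer that a T0 reading is meaningless.** The documents do not support that. Because of the MR-Linac simulation, the noise, bore and coil items may be answerable at T0. What stands is narrower: the time point is not the one in the text, and the item on gated delivery cannot be answered then.
- **A reader might infer that arm C data will be lost.** That too goes beyond the documents. The article names version 1.4 of the full protocol as the current version; neither it nor the case report form is shown. They may follow the text. Loss occurs only if the operational documents repeat the table and sites follow it over the text, so every figure here is conditional on that.
- **The instrument is minor.** It is absent from the sentence listing secondary objectives and from the secondary outcomes in the abstract, and no hypothesis or specific analysis is attached to it. The end-of-treatment reading in arm A is common to both versions. This stands, and it settles the severity.
- **Nothing proves that the text is the correct version.** On timing, the questionnaire's content favours the text. On arms, the article offers nothing beyond the contradiction. A request to reconcile is therefore justified; declaring the table wrong is not.

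One defence does not help. An article may leave detail to the full protocol, but here it states both versions and they conflict.

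**Conclusion.** The point holds as an internal inconsistency of low severity. Table 2 and Trial objectives contradict each other on both the arms and the first time point of the MR-Linac acceptance questionnaire. If the table were followed, at least 20 of roughly 51 MRgRT patients (about 39%) would contribute no acceptance data, and the first arm A reading would be off schedule and only partly answerable. This rests on two assumptions: that arm sizes come out near their targets, and that the table, not the text, drives collection. Neither can be checked from the article. The primary endpoint, the comparison of arm A with arm B, the sample size and the error rates are unaffected.

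**What to change.** Reconcile Table 2 with Trial objectives on arms and timing.

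- **If the text is what was intended:** relabel the row for arms A and C, remove the mark at T0, add a column or a footnote for the reading after the first fraction (the table currently has no place for it), and keep the mark at T2.
- **If the table is what was intended:** change the text to arm A and to the baseline visit, and say how the gated-delivery item is to be handled before any fraction.

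In either case, check that the full protocol and the case report form carry the same version. The cost is an edit to one table row or one sentence, plus a correction to the form if it has the same discrepancy. Under the first option, the 20 or more arm C patients would each complete a short questionnaire twice. Sample size, power and significance level do not change.

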### Statistical analysis

The sample size calculation is based on the primary comparison of the rates of gastrointestinal and hepatobiliary toxicity CTCAE of grade III or higher between the two treatment groups (arm A and B). A total of 62 patients are needed to assess non-inferiority by means of a Farrington-Manning test of MRgRT to ITV-SBRT with a power of 80% at a one-sided significance level of 10%, with allowance for 5% loss to follow-up and with the use of a clinically relevant non-inferiority margin of $$\delta$$ =10%, when assuming toxicity rates of pMRgRT = 2% and pITV-SBRT = 5%. It is expected that using a shifted Mantel–Haenszel type test for non-inferiority adjusting for the factor centre will yield an increased power.

To achieve a comparable arm C (BED < 100 Gy with ITV-SBRT) for the secondary objectives, the study will recruit patients until at least 20 analyzable patients are present in arm C. Due to the fact that patients in arm C are still treated with the best possible treatment, this approach is ethically justifiable.

Sample size calculation was performed using PASS 16.0.3.

The primary analysis will be based on the full analysis set (FAS) including all enrolled patients according to the intention to treat principle. The hypotheses for the primary analysis are$${H}_{0}:{p}_{\mathrm{MRgRT}}- {p}_{\mathrm{ITV}-\mathrm{SBRT }}\ge \delta vs. {H}_{1}:{p}_{\mathrm{MRgRT }}- {p}_{\mathrm{IITV}-\mathrm{SBRT }}<\delta$$

($$\delta$$ =10% non-inferiority margin), where $${p}_{\mathrm{MRgRT}}$$ and $${p}_{\mathrm{ITV}-\mathrm{SBRT}}$$ are the probabilities for an occurrence of a gastrointestinal and hepatobiliary toxicity CTCAE of grade III or higher for the MRgRT (arm A) and the ITV-SBRT (arm B) group, respectively. Non-inferiority of MRgRT as compared to ITV-SBRT will be tested at a one-sided significance level of α = 0.1 using a Mantel–Haenszel type test for non-inferiority adjusting for the stratum “centre”. Missing values for the primary outcome will be imputed using multiple imputation. Sensitivity analyses will be performed by means of conducting an analysis for the per-protocol (PP) population (based on those patients without major protocol violation).

Analysis of the secondary endpoints will also be based on the FAS. In order to compare all three treatment groups with regard to the primary endpoint, a (descriptive) Chi-squared test will be used. The secondary endpoints distant tumor control, overall survival and progression-free survival will be analyzed using Kaplan–Meier-Curves. The 1-year and 2-year survival rates as well as the median survival rate will be provided alongside two-sided 95%-confidence intervals. Descriptive pairwise log-rank tests stratified for “centre” will be conducted to compare all three treatment groups. The secondary endpoints local and locoregional control will be analyzed via cumulative incidence functions, taking the competing event death into account.

The other secondary endpoints and the patients’ characteristics will be displayed by descriptive measures. Descriptive pairwise comparisons between all three treatment groups will be performed. Continuous variables will be described using number of non-missing values, mean, standard deviation, median, Q1, Q3, minimum and maximum. For binary or categorical variables absolute and relative frequencies will be provided. Furthermore, two-sided 95%-confidence intervals will be calculated.

The safety analysis is based on the safety set including all patients who received one of the study treatments, and includes calculation of frequencies and rates of adverse and serious adverse events together with corresponding 95%-confidence intervals.

Further details of the analysis will be specified in the statistical analysis plan (SAP) which will be finalized before database closure. All analyses will be done using SAS version 9.4 or higher.

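### Distant tumor control is assigned to Kaplan–Meier while local and locoregional control use cumulative incidence with death as a competing event; if deaths are censored, distant failure will be overstated

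*Protocol article*

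**What the plan says.** All the analysis text at issue stands in one paragraph of the protocol article, in the Statistical analysis section.

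- Estimator for distant control: "The secondary endpoints distant tumor control, overall survival and progression-free survival will be analyzed using" Kaplan–Meier curves.
- Summary figures, in the sentence that follows: "The 1-year and 2-year survival rates as well as the median survival rate will be provided alongside two-sided 95%-confidence intervals".
- Comparison between arms: "Descriptive pairwise log-rank tests stratified for “centre” will be conducted to compare all three treatment groups".
- Estimator for the other two control endpoints: "The secondary endpoints local and locoregional control will be analyzed via cumulative incidence functions, taking the competing event death into account".

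The Trial objectives section lists the secondary efficacy endpoints as "local control (treated lesions), locoregional control (whole liver), distant tumor control, progression-free survival (PFS) and overall survival (OS". Distant control therefore sits next to the other two control endpoints and apart from the two survival endpoints. The article gives no event definition for it. Under Study visits and follow-up, visits continue "then every 6 months up to completion of a follow-up of at least 2 years (T8, T9".

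**The concern.** A patient who dies without distant failure can no longer have it, just as that patient can no longer have local failure. The plan recognises this for local and locoregional control. For overall and progression-free survival, death is conventionally part of the event, so Kaplan–Meier is suitable. Distant control has been grouped with the survival endpoints, although by name and listing it belongs with the control endpoints.

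Kaplan–Meier with deaths censored treats those who died as if they could still fail later at the same rate as those alive. Its complement then exceeds the proportion of patients who actually experience distant failure. Two things are at stake:

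- The 1- and 2-year distant rates and their intervals would be centred on the wrong quantity, and the median would come too early.
- Local, locoregional and distant failure would be reported side by side on different probability scales, so the pattern of failure could not be read across them. The size of the excess depends on mortality, so it could also differ between arms, including the non-randomized arm C.

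**Working it through.** **Figure to reproduce.** There is none. The article states no distant-failure rate, death rate or precision target for this endpoint.

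**Inputs.** The estimators and the 1- and 2-year time points come from the Statistical analysis section. The hazards are assumptions made for illustration: distant failure *h* = 0.5 to 0.7 per year, and death without prior distant failure *g* = 0.1 to 0.2 per year, both constant. The assumed *g* corresponds to a net 2-year risk of such a death of 1 − exp(−0.2) = 18% to 1 − exp(−0.4) = 33%.

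**Formulas.**
- Deaths censored: 1 − KM(t) = 1 − exp(−ht).
- Death as competing event: CIF(t) = h/(h+g) × [1 − exp(−(h+g)t)].

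**Example, h = 0.5, g = 0.2, t = 2.** 1 − KM = 1 − exp(−1.0) = 63.2%. CIF = (0.5/0.7) × [1 − exp(−1.4)] = 0.714 × 0.753 = 53.8%. The excess is 9.4 points.

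**All four corners.**

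| h | g | 1 − KM, 1 y | CIF, 1 y | Excess | 1 − KM, 2 y | CIF, 2 y | Excess |
|---|---|---|---|---|---|---|---|
| 0.5 | 0.1 | 39.3% | 37.6% | 1.8 | 63.2% | 58.2% | 5.0 |
| 0.5 | 0.2 | 39.3% | 36.0% | 3.4 | 63.2% | 53.8% | 9.4 |
| 0.7 | 0.1 | 50.3% | 48.2% | 2.2 | 75.3% | 69.8% | 5.5 |
| 0.7 | 0.2 | 50.3% | 46.2% | 4.2 | 75.3% | 64.9% | 10.4 |

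Excesses are in percentage points and were computed before rounding.

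**Median.** The Kaplan–Meier median is ln 2/h. The cumulative incidence reaches 50% at −ln[1 − 0.5(h+g)/h]/(h+g). For h = 0.5 and g = 0.2 these are 0.693/0.5 = 1.39 years and −ln(0.30)/0.7 = 1.72 years.

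**Sensitivity.** Let the 2-year 1 − KM run from 30% to 70% and the net 2-year risk of death without distant failure from 20% to 60%. The excess is then 2.9 to 20.0 points at 2 years and 0.9 to 8.1 points at 1 year. It is positive throughout. It is zero only if nobody dies without prior distant failure.

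**What is not affected.** With deaths censored, the planned centre-stratified log-rank test compares cause-specific hazards of distant failure, which is a legitimate comparison. Only the absolute rates and the median are open to challenge.

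**The case against.** The strongest objection is that the article never says deaths are censored for distant control. A reader might infer from the word Kaplan–Meier that they are and call this a proven error, but the text does not go that far. The endpoint is grouped with overall and progression-free survival, and the group is promised survival rates and a median. The authors name death as a competing event in the same paragraph, so they know the issue and the grouping may be deliberate. If death counts as an event, Kaplan–Meier is valid and the bias is zero. This stands as a limit on certainty. It does not remove the point, because an endpoint that counts deaths is distant-metastasis-free survival, not distant control, and needs that name and definition. Either reading calls for a correction.

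A second objection is that event definitions may sit in the full protocol or the analysis plan, neither of which is shown. It is true that the missing definition alone is no finding in a condensed article. But the article defers only detail ("Further details of the analysis will be specified in the statistical analysis plan (SAP) which will be finalized before database closure"). The choice of estimator is already made, and it differs without explanation from that for the two neighbouring endpoints.

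Third, the endpoint is secondary and the comparisons are descriptive. With about 31 patients in a randomized arm, a 95% interval around a rate of 60% is roughly ±1.96 × √(0.6 × 0.4/31) = ±17 points, and with 20 in arm C about ±21, wider than the illustrated bias. This rightly limits the priority. It does not excuse a systematic error in one direction when the estimated rate is the main result of a descriptive endpoint.

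**Conclusion.** The point holds as a conditional one. The plan handles distant control differently from the other two control endpoints without giving a reason. On the natural reading, in which deaths are censored, it will overstate distant failure at 1 and 2 years and place the median too early. The direction follows from the method whenever any patient dies without prior distant failure. The size does not follow from the document: about 5–10 points at 2 years and 2–4 at 1 year is an illustration under assumed constant hazards, not a forecast.

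Two stronger conclusions might be drawn, and the documents support neither. One is that the comparison of arms is invalid; the log-rank test remains sound for cause-specific hazards. The other is that the trial's main conclusion is at risk; the primary toxicity test and the sample size do not use this endpoint. The matter should be corrected, but it is confined to secondary, descriptive reporting.

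**What to change.** State how death is handled, in one of two ways.

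1. **Preferred, if distant control is meant as named:** move it into the sentence on local and locoregional control, estimate it by cumulative incidence (Aalen–Johansen) with death as the competing event, and report the 1- and 2-year cumulative incidences with 95% confidence intervals. Keep the descriptive centre-stratified log-rank test, labelled as a comparison of cause-specific hazards.
2. **If death is meant to count as an event:** keep Kaplan–Meier, but rename the endpoint distant-metastasis-free survival and define it so.

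Overall and progression-free survival stay as they are. The cost is one sentence in the protocol or analysis plan, which can be written before the plan is finalized. No new data, visits or patients are needed.
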